### Plans for collection, laboratory evaluation, and storage of biological specimens for genetic or molecular analysis in this trial/future use {33}

N/a. No biological specimens will be collected.

## Statistical methods

### Statistical methods for primary and secondary outcomes {20a}

The primary objective of the study is to determine whether BMI-adjusted ventilation strategies result in a reduction of driving pressure. Data are tested for normal distribution using the Shapiro–Wilk test. Differences between the intervention group and the control group are assessed with a two-tailed unpaired *t*-test for normally distributed continuous data and with the Mann–Whitney test for non-normally distributed continuous data. In addition, descriptive statistical analyses (mean ± standard deviation, median, interquartile range, and 95% confidence interval, if applicable) will be performed.

For secondary endpoints, to evaluate the changes in lung ultrasound score between the pre- and postoperative groups and between the intervention groups, a two-way ANOVA will be performed with the time point (preoperative/postoperative) as one independent variable and the study group (intervention/control) as the other independent variable. For categorical variables (hypotension events, number of patients requiring supplemental oxygen), Fisher’s exact test will be used. For the secondary endpoint “time-weighted average of hypotension events,” the area under the threshold of 65 mmHg (AUC) for each event will be calculated by summing the difference between MAP and the threshold, multiplied by the duration of the event. Total AUC will be divided by the observed time, which varies by patient. This results in a time-weighted average of hypotension per patient.

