## Interventions

### Explanation for the choice of comparators {6b}

In normal weight patients, a PEEP setting of 5 mbar is considered as clinical standard. With an increasing number of overweight patients, a weight-adapted PEEP adjustment may be necessary. To be able to clinically apply optimal and standardized ventilation parameters for individual, weight-adjusted ventilation, an easy-to-apply calculation method is needed. Thus, we consider a comparison between a control group with standard therapy (PEEP 5 mbar) and an intervention group (PEEP BMI/3 mbar) to be useful. The same inclusion and exclusion criteria will be used to recruit the intervention and control group.

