### Outcomes {12}

The primary endpoint of this trial is the difference in driving pressure (ΔP) between the intervention and control group during general anesthesia in endotracheal intubation and volume-controlled ventilation (VCV). Secondary endpoints include:

Mechanical Power of ventilation (elastic-dynamic, tidal and total).Compliance of the respiratory system.Intraoperative fluid requirements.Average intraoperative vasopressor requirements (µg/kg/min).Number of intraoperative hypotension events (MAD < 65 mmHg for > 1 min).Time-weighted average of hypotension.Number of alveolar recruitment maneuvers (to be performed if SpO_2_ < 90% with FiO_2_ > 60%).SpO_2_ after arrival in recovery room (without oxygen insufflation).Number of patients with indication for oxygen insufflation (to maintain SpO_2_ ≥ 90%).Change in lung aeration score between before surgery and after arrival in recovery room(determined by lung ultrasound).Overall postoperative pulmonary complications.

For further clarification see, Table 1 (“Outcome Definition”).

**Table 1 Tab1:** Outcome definition

**Domain**	Respiratory mechanics	Rescue therapy	Hemodynamics	Postoperative status
Specific measures	• Driving pressure • Mechanical power of ventilation (elastic-dynamic, tidal, and total) • Compliance of respiratory system	• Number of alveolar recruitment maneuvers	• Intraoperative fluid requirements • Average intraoperative vasopressor requirements • Number of intraoperative hypotension events • time-weighted average of hypotension	• SpO_2_ after arrival in recovery room • Number of patients with additional oxygen insufflation^a^ • Change in lung aeration score
Specific metric	Difference between control and intervention group	Difference between control and intervention group	Difference between control and intervention group	Difference between control and intervention group
Method of aggregation	Mean + SD (parametric data) or Median/IQR (non-parametric data)	Mean + SD (parametric data) or Median/IQR (non-parametric data)	Mean + SD (parametric data) or Median/IQR (non-parametric data)	Mean + SD (parametric data) or Median/IQR (non-parametric data) and four-square table^a^
Time point	Intraoperative	Intraoperative	Intraoperative	Postoperative

Outcomes are defined following the framework of Saldanha et al. [20]

^a^Four-square table is only used as method of aggregation for “number of patients with additional oxygen insufflation”

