### Sample size {14}

Sample size calculation was performed with G*power 3.1 Software [13]. Assuming a mean (± SD) ΔP of 10 (± 3) mbar at PEEP = 5 mbar and a mean ΔP of 8 (± 2) mbar at PEEP = BMI/3 mbar, *α* = 0.05, 1 − *β* = 0.8, G*Power yielded a required sample size of *n* = 54 (27 per group) patients. The anticipated effect size is based on the results previously published by Pereira et al. [10]. To compensate for refusal, technical difficulties, or possible dropouts, we will increase the sample size by 10%, resulting in a total sample size of 60 patients.

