### Methods for additional analyses (e.g., subgroup analyses) {20b}

Not applicable, further analyses are not planned.

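### A normality pre-test chooses between a mean comparison and a rank test for the primary endpoint, so the effect measure is not fixed in advance; BMI, which sets the treatment contrast, goes unused

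*Protocol article*

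**What the plan says.** Outcomes {12} defines the endpoint: "The primary endpoint of this trial is the difference in driving pressure (ΔP) between the intervention and control group". For the analysis, Statistical methods {20a} says "Data are tested for normal distribution using the Shapiro–Wilk test". It then prescribes a "two-tailed unpaired *t*-test for normally distributed continuous data" and otherwise a comparison "with the Mann–Whitney test for non-normally distributed continuous data". No other between-group test is given for continuous data, so this rule governs the primary endpoint. Table 1 under Outcomes {12} carries the same switch into the summaries: mean with SD, or median with IQR.

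Sample size {14} is stated in means: "Assuming a mean (± SD) ΔP of 10 (± 3) mbar at PEEP = 5 mbar" and "a mean ΔP of 8 (± 2) mbar at PEEP = BMI/3 mbar", giving 27 per group and 60 in total after a 10% allowance.

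Under Intervention description {11a}, PEEP is BMI/3 in one arm and 5 mbar in the other. Height and weight are measured after consent, and allocation follows after induction, so BMI is known before randomisation. Eligibility {10} excludes only BMI above 60. No covariate is named in {20a}, and Methods for additional analyses {20b} reads: "Not applicable, further analyses are not planned".

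**The concern.** A t-test and a Mann–Whitney test answer different questions. The first concerns the difference in means. The second concerns the chance that a patient in one arm has a higher value than a patient in the other, and it can be read as a shift in location only if the two distributions share a shape. The plan's own SDs of 3 and 2 say that they do not. Under the gated rule, nobody can say before the data are seen which quantity the primary p-value will refer to, although the trial was powered for only one of them. This is not a detail left to a separate analysis plan, because the protocol states the gate itself.

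The second part concerns efficiency. The treatment is a function of BMI, and the case for it in {6b} rests on BMI: "With an increasing number of overweight patients, a weight-adapted PEEP adjustment may be necessary". A baseline variable that fixes the size of each patient's contrast, and may also predict ΔP, is available at no extra cost and is not used.

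**Working it through.** **1. The plan's own figure.** Inputs from {14}: means 10 and 8, SDs 3 and 2, α = 0.05, power 0.80.
- Pooled SD = √((3² + 2²)/2) = √6.5 = 2.55. Effect size d = 2/2.55 = 0.784.
- Two-sided t-test, noncentrality d·√(n/2): power is 0.792 at n = 26 per arm and 0.808 at n = 27.
- So 27 per arm and 54 in total reproduce exactly, and 54 × 1.1 = 59.4 rounds up to 60. The design is a two-sided comparison of means.

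**2. Do the branches test the same thing?** Take equal means of 10, SDs of 3 and 2, and a log-normal shape (assumed; the documents give no shape).
- Medians are 10/√(1 + 0.09) = 9.58 and 10/√(1 + 0.04) = 9.81.
- The log-variances are ln 1.09 = 0.0862 and ln 1.04 = 0.0392. P(control value > intervention value) = Φ((ln 9.58 − ln 9.81)/√(0.0862 + 0.0392)) = Φ(−0.066) = 0.47.
- The mean difference is zero, but the Mann–Whitney quantity is not at its null value of 0.5.

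**3. How the gated rule behaves.** Simulation, 20,000 replicates per row. Assumptions: Shapiro–Wilk at 0.05 in each arm, with a switch if either rejects; pooled-variance t-test. The text specifies neither.

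| Setting (control/intervention) | Shape | Switch to Mann–Whitney | Gated rule | Pooled t, no gate | Welch, no gate |
|---|---|---|---|---|---|
| Equal means, 27/27 | normal | 10% | 5.0% | 4.9% | 4.8% |
| Equal means, 27/27 | log-normal | 44% | 6.9% | 5.3% | 5.3% |
| Equal means, 20/30 | normal | 10% | 7.3% | 7.0% | 5.0% |
| Equal means, 20/30 | log-normal | 38% | 8.0% | 7.0% | 5.2% |
| Equal means, 30/20 | normal | 10% | 3.6% | 3.5% | 4.9% |
| Equal means, 30/20 | log-normal | 45% | 5.0% | 3.6% | 4.9% |
| Means 10 and 8, 27/27 | normal | 10% | 80.9% | 81.1% | 80.9% |
| Means 10 and 8, 27/27 | log-normal | 49% | 80.6% | 82.8% | 82.7% |

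The percentages in the last three columns are rejection rates. The 27/27 log-normal figure of 6.9% varies with the run; other runs gave 6.3 to 6.7%. At the design effect, the t-test and Mann–Whitney disagree on significance in 6.5% (normal) and 7.4% (log-normal) of trials.

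**4. BMI.** The PEEP contrast is BMI/3 − 5: 0 mbar at BMI 15, 3.3 at 25, 5 at 30, 8.3 at 40 and 15 at 60.

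The documents give no correlation ρ between BMI and ΔP, so a range is assumed, with one common slope in both arms. Residual SD = 2.55·√(1 − ρ²).
- ρ = 0: d = 0.784, power 0.81 at 27 per arm.
- ρ = 0.3: SD 2.43, d = 0.822, power 0.84; 50 patients would give 80%.
- ρ = 0.5: SD 2.21, d = 0.906, power 0.90; 42 patients would give 80%.

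**The case against.** Four points can be made for the plan as written.

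- **Little numerical harm as planned.** This stands. Allocation is 1:1 in permuted blocks. At 27/27 the gated rule holds 5.0% with normal data and about 6.5% with a skewed shape that is itself an assumption, and power stays near 80%. A reader might infer from the 20/30 rows that the pre-test seriously inflates type I error. The documents do not support that. From a target of 60, that split needs all 10 losses to fall in the arm with the larger assumed SD. Most of the excess also appears with an ungated pooled t-test (7.0%), and the opposite imbalance gives about 4 to 5%. The text says only that the t-test is unpaired, so pooling is an inference.
- **The unadjusted comparison is valid.** This stands too. Randomisation makes it unbiased, and the stated sample size is correct for it. A reader might infer that leaving BMI out biases the result, or that the trial cannot answer its own question. Neither follows: the objective in {7} is whether the BMI rule lowers ΔP compared with 5 mbar, and one randomised mean difference answers that.
- **The gain from BMI is speculative.** This stands in part. The studies summarised in the Background {6a} link BMI to the PEEP that is required, not to ΔP. The gain could be near zero, but the cost is one degree of freedom.
- **Both mean and median will be described.** {20a} does promise such summaries, with a confidence interval where applicable. That helps the reader, but it does not say which quantity the primary test concerns.

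**Conclusion.** The point holds as one of specification and efficiency. The gate leaves the primary effect measure undecided until the data are in, although the trial is powered on a mean difference and its assumed SDs imply that the two branches differ in what they test. The choice would go to Mann–Whitney in about 10% of trials with normal data and 44 to 49% under the assumed log-normal shape. The two tests would disagree on significance in about 7% of trials at the design effect.

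The effect on type I error is small at the planned allocation. It reaches about 7 to 8% only if the lower-variance arm ends clearly larger and the t-test pools variances.

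Leaving out BMI costs possible precision: power of 84 to 90% instead of 81% if the within-arm correlation is 0.3 to 0.5, which is assumed. It causes no bias. A reader might also conclude that an analysis by BMI is required. The documents do not make the question of who benefits an objective, and {20b} openly declines such analyses.

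**What to change.** In {20a}, remove the Shapiro–Wilk gate for the primary endpoint and name one analysis: a linear model of per-patient ΔP on group, with centred BMI as covariate and heteroscedasticity-robust standard errors (HC3, for example), reporting the mean difference with its 95% confidence interval. Keep Mann–Whitney as a labelled sensitivity analysis. Amend the sentence in {20b} and the mean-or-median entry for ΔP in Table 1 to match.

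A group-by-BMI model is optional. If added, it should be called exploratory, because it will be imprecise with 60 patients.

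The cost is wording and one degree of freedom, with no more patients and no new measurements. The planned 54 evaluable patients suffice even if BMI explains nothing. The change should be dated before ΔP is examined by group.

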### Intervention description{11a}

Only patients who provide consent will be included in the study. After obtaining written informed consent, total height, weight, and waist to hip ratio will be measured. On the day of surgery, a preoperative lung ultrasound examination will be carried out immediately before the patient is admitted to the operating room and the lung aeration score will be calculated as described in [12]. After induction of general anesthesia, patients will be assigned to a group by opening a sealed envelope containing the allocation. All patients will be ventilated in a volume-controlled mode (VCV) with constant inspiratory flow at a tidal volume of 7 ml per kg predicted body weight (PBW), with an I:E ratio of 1:2 and an inspiratory pause of 30%. PBW will be calculated using the NIH-NHLBI ARDS Network formula. ♂: PBW (kg) = 50 + 0.91 (height (cm) − 152.4) and ♀: PBW (kg) = 45.5 + 0.91 (height (cm) − 152.4) [19].

In the intervention group, PEEP will be adjusted to a value of BMI/3 mbar for the duration of general anesthesia. In the control group, PEEP will be set at a fixed value of 5 mbar for the duration of general anesthesia. Sustained-inflation recruitment maneuvers will be performed after disconnection of ventilator circuit and in case of a drop in oxygen saturation below 90% despite ventilation with more than 60% of oxygen, with an airway pressure of 20 mbar above PEEP for 10 s in the intervention group and with an airway pressure of 30 mbar for 10 s in the control group. The lung ultrasound data will be stored anonymously and evaluation of the ultrasound images for calculation of lung aeration score will take place without knowledge of the group allocation (Fig. 1).

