## Discussion

This study aims to evaluate whether intraoperative PEEP adjustment according to BMI is safe, reduces driving pressure by increasing respiratory system compliance, and prevents loss of lung aeration as assessed by lung ultrasound in comparison to a standardized PEEP setting of 5 mbar.

Induction of general anesthesia and the subsequent loss of spontaneous respiration result in decisive changes in lung physiology, leading to atelectasis, reduced gas exchange, and reduced end-expiratory lung volume. These effects are partly dependent on body weight and might be more pronounced in obese patients, indicating the need for individualized ventilation strategies [9]. Nevertheless, the individualized approach must still be clinically feasible. Although the results may not be as ideal as with more elaborate methods of PEEP adjustment such as electrical impedance tomography or transpulmonary pressure measurement, a simple tool such as the rule of thumb PEEP = BMI/3 could represent a clinically feasible compromise between individualization and applicability.

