Several previously conducted studies propose an association between high ΔP, high elastic-dynamic mechanical power (the product of ΔP, tidal volume, and respiratory rate) and unfavorable outcomes for patients with acute respiratory distress syndrome [17, 18]. For patients undergoing mechanical ventilation during general anesthesia, the available evidence suggests that a ventilation strategy that leads to a reduction in ΔP also reduces the risk of postoperative pulmonary complications [5]. For this reason, ΔP was chosen as primary endpoint in this trial. To further analyze the effect of PEEP adjustment according to BMI, respiratory system compliance, the different components of mechanical power (elastic-static, elastic-dynamic, resistive, total, tidal), intraoperative hemodynamics, postoperative oxygen requirements, and the number of intraoperative recruitment maneuvers required to maintain SpO_2_ > 90% with FiO_2_ < 60% will be recorded.

Available data suggest that 1 mbar increase in ΔP leads to a 16% relative risk increase for postoperative pulmonary complications (odds ratio for one unit increase of driving pressure 1.16) [5]. With an incidence of postoperative pulmonary complications around 5% in a mixed surgical population [1] and an assumed reduction of driving pressure by 1–2 mbar with PEEP adjusted according to BMI, a sample size of several thousand patients would be required to show a statistically significant reduction in postoperative pulmonary complications with our strategy. We therefore chose driving pressure as easy to measure and clinically relevant surrogate outcome parameter for our single-center trial assuming that a ventilation strategy that leads to a reduction in ΔP will ultimately reduce the risk of postoperative pulmonary complications in larger populations.

However, as this is the subject of the study, we cannot exclude with certainty that ΔP and the associated risk of postoperative pulmonary complications could also be increased with the ventilation strategy studied. Further limitations include that results may not be applicable to procedures with altered intrathoracic or intraabdominal pressures, such as laparoscopic or thoracic procedures or patient’s positions other than flat supine. Due to the study design the occurrence of PPCs could not be evaluated, this would have required a significantly higher number of patients. Thus, this aspect should be considered in further studies.

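### Compliance and elastic-dynamic power scale with predicted body weight by design but are compared without adjusting for it, an avoidable loss of precision on secondary endpoints

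*Protocol article*

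**What the plan says.** The section on statistical methods for primary and secondary outcomes {20a} sets one rule for continuous data. After a Shapiro–Wilk test, "Differences between the intervention group and the control group are assessed with a two-tailed unpaired" t-test if the data look normal, and with a Mann–Whitney test otherwise. Under additional analyses {20b} the article adds that "further analyses are not planned".

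Outcomes {12} lists "Mechanical Power of ventilation (elastic-dynamic, tidal and total" components) and "Compliance of the respiratory system" as secondary endpoints. Table 1 gives their metric as "Difference between control and intervention group". Neither is indexed to body size.

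The intervention description {11a} sets ventilation in both arms with "constant inspiratory flow at a tidal volume of 7 ml per kg predicted body weight (PBW"), where PBW is computed from height and sex. The Discussion defines "elastic-dynamic mechanical power (the product of ΔP, tidal volume, and respiratory rate"). It also gives as an aim to find out whether the strategy "reduces driving pressure by increasing respiratory system compliance".

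**The concern.** When tidal volume is a fixed multiple of PBW, a tall man and a short woman with the same ΔP have very different compliance and elastic-dynamic power. The difference says nothing about PEEP. An unadjusted comparison treats it as noise. ΔP does not carry this multiplier, because its tidal volume has already been scaled to PBW.

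What is at stake is precision. The trial could find a clear difference in ΔP and no clear difference in compliance, partly because of how height and sex vary among 60 patients. The randomisation sections describe no stratification, so a chance imbalance in height or sex would shift both endpoints. The value needed to remove this noise is already calculated for each patient in order to set the ventilator.

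**Working it through.** **Inputs from the protocol article.** ΔP 10 (SD 3) versus 8 (SD 2) mbar, two-sided α 0.05, power 0.80, 27 per arm, raised to 60 in total (Sample size {14}). Tidal volume 7 ml/kg PBW, and the PBW formula ({11a}).

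**Assumed, not in the article.** Mean PBW 65 kg, SD 7, 10 or 12 kg; PBW independent of ΔP; respiratory rate constant, or with a coefficient of variation (CV) of 10–15%. Compliance is taken as tidal volume / ΔP.

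**1. The plan's own figure.** Pooled SD = √((3² + 2²)/2) = 2.55 and d = 2/2.55 = 0.784. The noncentral t gives 27 per arm with 80.8% power. The stated 54 reproduces, and so does 60 after the 10% increase.

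**2. How body size enters.**
- Compliance = 7 × PBW / ΔP
- Elastic-dynamic power = ΔP × 7 × PBW × rate

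As an illustration with assumed heights, a man of 185 cm has PBW 50 + 0.91 × 32.6 = 79.7 kg, and a woman of 165 cm has 45.5 + 0.91 × 12.6 = 57.0 kg. At the same ΔP of 10 mbar their compliances are 55.8 and 39.9 ml/mbar, a ratio of 1.40. The planned treatment effect corresponds to a ratio of about 10/8 = 1.25.

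**3. Share of variance due to PBW.** The CVs of ΔP are 3/10 = 0.30 and 2/8 = 0.25, with mean square (0.0900 + 0.0625)/2 = 0.076. For a product or quotient of independent terms with constant rate, R² ≈ CV²(PBW) / (CV²(PBW) + 0.076).

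| PBW SD | CV | CV² | R² |
|---|---|---|---|
| 7 kg | 0.108 | 0.012 | 0.13 |
| 10 kg | 0.154 | 0.024 | 0.24 |
| 12 kg | 0.185 | 0.034 | 0.31 |

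**4. What that costs by formula.** Adjusting divides the noncentrality by √(1 − R²) and uses 2n − 3 degrees of freedom. Points gained:

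| R² | Unadjusted power 50% | Unadjusted power 80% |
|---|---|---|
| 0.10 | 4.2 | 3.9 |
| 0.20 | 9.1 | 7.9 |
| 0.30 | 14.9 | 11.7 |

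**5. Simulation.** 20,000 runs, 27 per arm, lognormal ΔP with the plan's means and SDs, rate CV 10%. An unadjusted t-test is compared with ANCOVA on PBW, both on the original scale.

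| Endpoint | PBW SD 7 / 10 / 12 kg: unadjusted | Adjusted | Gain in points |
|---|---|---|---|
| Compliance | 67 / 62 / 57% | about 73% | 5 / 10 / 15 |
| Elastic-dynamic power | 72 / 66 / 62% | about 75% | 4 / 9 / 13 |

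With gamma-distributed ΔP and constant rate, the gains for PBW CV 0.12–0.20 are 5 to 14 points (compliance) and 6 to 16 points (elastic-dynamic power). At CV 0.10 they are 3 to 4 points.

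**6. Smaller effect.** The Discussion also speaks of a reduction of 1–2 mbar. For 1 mbar (10 versus 9, SD 2.5 assumed in the intervention arm) the gain is only about 1 to 6 points, because power is about 15–25% either way.

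**The case against.** **The planned test is valid.** Chance imbalance in height or sex is covered by its type I error, and raw compliance in ml/mbar is a legitimate, familiar quantity. These are secondary endpoints of a trial that calls itself a pilot and states power only for ΔP. This stands, and it limits the point to efficiency.

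**Covariates could be left to an analysis plan that is not shown.** This stands only in part. The article names the test for these endpoints, so the point concerns a stated choice. The sentence excluding further analyses stands under additional and subgroup analyses, so it does not by itself rule out a covariate.

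**A loss of 20 points or more might be inferred.** That figure is not due to body size alone. A log-scale model adjusted for PBW reaches 79–80% for compliance, but part of that gain comes from the transformation. Nor is the log scale uniformly better. With gamma ΔP, PBW SD 7 kg and rate CV 15%, it gives 63% for elastic-dynamic power against 65% for the plain t-test.

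**The plan's comparator is not always a t-test.** With lognormal ΔP, about half of simulated trials go to Mann–Whitney, and planned power for compliance is 72 / 64 / 61%. Original-scale ANCOVA at about 73% then gains 73 − 72 = 1, 9 and 12 points. The routing wins back some power lost to skewness, not the part lost to body size. Indexing to PBW keeps the routing. With the same inputs (4,000 runs), it gave 78 / 78 / 77% for compliance per kg PBW against 72 / 66 / 60% for raw compliance.

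**A reader might infer that a discordant compliance result would be misread as evidence about mechanism.** The article sets no rule for interpreting compliance beside ΔP. It states only an aim in the Discussion, so misreading is a possibility and no more.

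**Conclusion.** The point holds as an optional gain in efficiency. Compliance and elastic-dynamic power contain PBW as a factor because of how tidal volume is set, and the stated comparison leaves that variation in the error term. Like for like on the original scale, the cost is roughly 4 to 15 points of power at the planned effect with 27 per arm.

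The link to PBW is arithmetic; the size is not. It rests on an assumed PBW SD of 7–12 kg around 65 kg and on independence of PBW and ΔP. A more variable respiratory rate reduces the gain for mechanical power. The article gives no PBW spread, no respiratory rate and no correlation. Tidal and total power were not simulated, so no figure is claimed for them.

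The documents do not support reading this as bias, as an invalid test or as a fault in the primary analysis. ΔP and N = 60 are untouched. PBW-adjusted compliance is also nearly the reciprocal of ΔP, so the better-powered comparison would largely repeat the primary result and would not confirm a mechanism independently.

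**What to change.** In {20a}, add that compliance and the mechanical power components are analysed by ANCOVA with study group and PBW, PBW being a prespecified covariate, and that the adjusted difference is reported with its 95% CI. Alternatively, index these endpoints to PBW. This is the simpler choice if the Shapiro–Wilk routing is to stay. Keep the raw values as descriptive summaries. A log scale is optional, and removing the body-size noise does not require it.

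Add one statement: with tidal volume fixed per kg PBW, PBW-adjusted compliance largely restates ΔP and is not independent confirmation of how the strategy works.

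Cost: a sentence or two of wording, and one degree of freedom if ANCOVA is used. No new data are needed, since height is measured and PBW is already calculated.

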### Participant timeline {13}

Within the week before surgery, patients will visit the pre-medication outpatient clinic. Participants will be screened and, if eligible, will be asked to provide written informed consent to participate in the study. Only patients who provide consent will be included in the study. After obtaining consent, total height, weight, and waist to hip ratio will be measured. On the day of surgery, a preoperative lung ultrasound examination will be carried out immediately before the patient is admitted to the operating room. After induction of general anesthesia, patients will be randomized by opening a sealed envelope. The protocol is then carried out accordingly for the control group or for the intervention group. After extubation, patients will be transferred to the recovery room. A postoperative lung ultrasound examination will be carried out. Additional oxygen will be applied if oxygen saturation drops below 90% breathing room air. Patients will be discharged from the recovery room according to routine clinical criteria (oxygen saturation > 90% or similar to preoperative value breathing room air, hemodynamic stability, patient awake and oriented, sufficient pain control). Data collection ends after patient is discharged; no further follow-up is needed (Fig. 2).

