Lung ultrasound has found widespread integration in clinical routine regarding the assessment of lung aeration in patients with dyspnea and acute respiratory failure [14] and is an established and readily available noninvasive method tool for the detection of postoperative pulmonary complications. Lung ultrasound allows early detection of changes in lung structure that are typical of PPCs, such as an increase in lung density due to atelectasis or effusions [15]. However, visualization of a single examination cannot be considered specific enough for diagnosis, thus it is deemed useful to perform an initial examination preoperatively before intubation and a follow-up examination postoperatively after termination of mechanical ventilation [12]. To establish longitudinal comparability and classify the severity of lung structural change, a standardized lung ultrasound scoring system should be applied [16]. The lung aeration score, based on the BLUE protocol [14], represents a validated score that has been successfully applied several times. Sonography is performed on spontaneously breathing patients in six regions per hemithorax, 0 to 3 points are assigned to each region according to the observed lung ultrasound pattern, and a sum is calculated. To evaluate the immediate postoperative outcome, oxygen saturation, required oxygen insufflation, and duration of stay in the recovery room will be analyzed as secondary outcome parameters. The length of stay in the recovery room will usually be half of the operating time and can be terminated as soon as the patient is hemodynamically and respiratory stable without further interventions.

To ensure reliable data collection and analysis, the team collecting the data was trained in the performance of lung ultrasound and the analysis team was trained in the use of the lung ultrasound score before the start of the study, using 20 sample patients. Therefore, to reduce examiner bias and prevent potential sources of error, acquisition and assessment of ultrasound images will always be performed by at least two different researchers. Lung ultrasound analyzers are blinded to group assignment and other clinical data.

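### The lung aeration score is to be analysed by a two-way ANOVA that neither states that time is within-patient nor names the group-by-time contrast as the treatment test.

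*Protocol article*

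**What the plan says.** Section {12} (Outcomes) lists as a secondary endpoint "Change in lung aeration score between before surgery and after arrival in recovery room". Table 1 gives the metric for this domain as the difference between the control and intervention groups.

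Each patient is scanned twice. Under Participant timeline {13}, "a preoperative lung ultrasound examination will be carried out immediately before the patient is admitted to the operating room"; after transfer to the recovery room, "A postoperative lung ultrasound examination will be carried out". The Discussion gives the reason: it is useful to "perform an initial examination preoperatively before intubation and a follow-up examination postoperatively after termination of mechanical ventilation".

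Section {20a} describes the analysis as one of "changes in lung ultrasound score between the pre- and postoperative groups and between the intervention groups". For this, "a two-way ANOVA will be performed with the time point (preoperative/postoperative) as one independent variable and the study group (intervention/control) as the other" factor. No patient term, repeated-measures factor or baseline covariate is named, and no model term is designated as the treatment test. Section {20b} plans no further analyses.

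**The concern.** The endpoint section describes a paired quantity: each patient's change, compared between arms. The analysis section describes a model with two factors and speaks of the time points as groups, which is how one would describe separate samples. Taken at face value, the model puts all scans into a single residual with no patient effect. Two scans of one patient on one scale will almost certainly be positively correlated, so that residual is wrong for every test in the table.

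The second gap is that a two-way ANOVA yields three tests (time, group, interaction) and the plan does not say which one answers the treatment question. Only the interaction matches the endpoint in section {12}. The group main effect averages the preoperative score, taken before randomisation, with the postoperative one, so it carries half of any treatment effect.

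The lung score is the one outcome that the article describes as assessed blind to allocation, and the Discussion lists preventing loss of aeration among the trial's aims. A real benefit could be missed by an over-conservative interaction test, or a chance difference reported from a liberal main-effect test.

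**Working it through.** **The plan's own figure.** The article gives no sample size, SD or effect for the lung score. Its sample size for driving pressure does reproduce: pooled SD = √((3² + 2²)/2) = 2.55 and d = 2/2.55 = 0.784; a two-sided t-test at 5% has 80.8% power with 27 per arm (79.2% with 26). So n = 27 per arm is used below.

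**Assumptions, not from the documents.** Normally distributed scores; the same SD s at both times and in both arms; pre-post correlation ρ = 0.3, 0.5 or 0.7; treatment effect 0.7 s on the postoperative score.

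**Interaction (difference in change).** Its true variance is 4s²(1 − ρ)/n. An ordinary two-way ANOVA uses 4s²/n on 4n − 4 = 104 df, with critical value 1.983. The actual two-sided error is therefore about 2Φ(−1.983/√(1 − ρ)):
- ρ = 0.3: 1.983/0.837 = 2.37, giving 1.8%
- ρ = 0.5: 1.983/0.707 = 2.80, giving 0.5%
- ρ = 0.7: 1.983/0.548 = 3.62, giving 0.03%

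Simulation, which also allows for the estimated residual variance, gives about 2% / 0.6% / 0.1%. The time effect behaves the same way.

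**Group main effect.** Its true variance is s²(1 + ρ)/n; the ordinary ANOVA uses s²/n. The error is about 2Φ(−1.983/√(1 + ρ)):
- ρ = 0.3: 1.983/1.140 = 1.74, giving 8.2%
- ρ = 0.5: 1.983/1.225 = 1.62, giving 10.5%
- ρ = 0.7: 1.983/1.304 = 1.52, giving 12.8%

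Simulation gives about 8% / 11% / 13%.

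**Power for a 0.7 s effect.** The unpaired interaction is significant only if the observed difference in change exceeds about 1.983 × √(4/27) s = 0.763 s. That is more than the assumed effect, so power stays below one half whatever ρ is. The other two analyses use their correct standard errors: √(4(1 − ρ)/27) s = 0.322 / 0.272 / 0.211 s for the paired change, and √(2(1 − ρ²)/27) s = 0.260 / 0.236 / 0.194 s for ANCOVA.

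| Analysis | ρ = 0.3 | ρ = 0.5 | ρ = 0.7 |
|---|---|---|---|
| Interaction, unpaired | 42% | 41% | 39% |
| Interaction or change score, pairing modelled | 57% | 71% | 90% |
| ANCOVA on preoperative score | 75% | 82% | 94% |

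With pairing modelled, simulated type I error of the interaction is about 5% throughout. At ρ = 0 the paired and unpaired tests agree.

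**Group main effect, even when correctly modelled.** The effect is 0.35 s with standard error √((1 + ρ)/27) s = 0.219 / 0.236 / 0.251 s. Power is about 35% / 31% / 28%.

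**The case against.** The text nowhere says that time is a between-patient factor. A reader might infer it from the term independent variable, but that term means a predictor or factor and says nothing about independence of the observations. A two-way ANOVA on time and group can be run as a mixed ANOVA with time within patient. The full protocol and any SAP are not shown, and an article may leave the error term to them. This stands: it cannot be concluded that the wrong model will be fitted.

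The endpoint definition and Table 1 also point to a between-arm comparison of change, which is the interaction. A reader might infer that the group main effect is the planned efficacy test, but the plan does not nominate it. What remains is that section {20a} does not carry the endpoint definition through to a named test.

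Finally, one might present 41% against 82% as the cost of ignoring the pairing. That is too strong. At ρ = 0.5, pairing accounts for the step from 41% to 71% (30 points), and ANCOVA's extra efficiency for the step from 71% to 82% (11 points). At ρ = 0.3 the steps are 15 and 18 points. Analysing paired change is valid in a randomised trial, so leaving out the baseline covariate costs efficiency but is not an error.

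**Conclusion.** The concern holds as a defect of specification. Section {20a} fixes a model without saying that time is within-patient and without tying the endpoint to a model term. Followed literally, it gives an interaction test that is too conservative (about 2% down to 0.1% instead of 5%) and a group main effect that is too liberal (about 8% to 13%) for ρ from 0.3 to 0.7. The directions hold for any positive correlation. The sizes rest on the assumed ρ, equal SDs and 27 per arm, and the power figures also on the assumed 0.7 SD effect.

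Under a correctly fitted mixed ANOVA the error-rate problem disappears. The treatment test would still be undesignated and the preoperative score unused as a covariate. The matter concerns one secondary endpoint; the driving-pressure analysis and the sample size of 60 are not touched.

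**What to change.** Replace the two-way ANOVA in section {20a} with an ANCOVA: postoperative lung aeration score on study group, with the preoperative score as covariate, reporting the adjusted mean difference with its 95% CI.

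At minimum, state that time is a repeated, within-patient factor and that the group-by-time interaction (equivalently, the between-group comparison of change) is the treatment test. In either case, say that the group main effect is not used to judge efficacy, and reword the sentence that calls the time points groups.

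The cost is a wording change. Both scans are already scheduled for every patient, so no new data are needed.
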